### The trial flow

When included in the trial, a baseline questionnaire is handed to the participant. Evidence from randomised trials suggests that in questionnaire design, ‘shorter is better’ 
[26]. Thus, attempts have been made to make the baseline questionnaire as short as possible. However, given the conceptual broadness of ‘self-management’, the questionnaire compiles items covering exposures, susceptibility, knowledge, medical adherence and self-efficacy. Immediately after randomisation, an initial basic counselling is given to participants in the intervention group. An appointment of the subsequent nurse-led consultation is offered to be conveniently executed in timely relation to the next medical consultation. Also, the patient is offered to choose between patient self-management books of either physical or electronic form. The trial flow is displayed in Figure 
1.

**Figure 1 F1:**
[figure not shown]
Trial flow chart.

### Trial intervention

The trial aims at intervening multi modally through initiatives which separately may be expected to support patient self-management and to be beneficial to the hand eczema prognosis 
[10,13,15,27-29]. The intervention is named The Healthy Skin Clinic in order to emphasise that self-management of hand eczema is more than medication adherence thus also involves health promotion. The Healthy Skin Clinic complies with usual clinical practice aiming to provide the patient with a systematic, yet individually, based counselling programme including a support module. The Healthy Skin Clinic is maintained by experienced nurses within the dermatological specialty along with the investigator (setting A), or by an experienced health care assistant supervised by the investigator and a dermatologist (setting B). A high level of team communication is conducted in order to provide commonality of the intervention.

The intervention is founded upon three concurrent elements. Firstly, a SKIN-profile is generated by responses from the baseline questionnaire. The profile is descriptive of the patient regarding susceptibility; knowledge; co-morbidity; social support; and necessary precautions i.e. allergies and aggravating irritant factors. One significant purpose of generating the profile is to clarify the multifactorial aetiology of (the persistence of) chronic hand eczema thus direct focus to the relevant areas in the following nurse-led consultation.

Secondly, a patient self-management book is offered. The book is a dynamic tool, which is launched in an electronic form, i.e. a secure website. Patients, with no possibilities of using information technology, will be handed over a physical book containing the same features. The patient self-management book contains information material which is tailored to the SKIN-profile. In addition, tools for self-monitoring of the disease are offered with the purpose of encouraging the patient to take a more proactive role in the course.

Finally, in addition to the nurse-led consultation, support to self-management through asynchronous communication and networking is offered. The online users may facilitate contact to either the intervention team or to other trial participants by use of the website. To the users of the physical self-management book a telephone based hotline is offered. An overall graphical depiction of the Healthy Skin Clinic intervention is presented in Figure 
2 as this is a way proposed to clarify the content of complex interventions 
[30].

**Figure 2 F2:**
[figure not shown]
**Graphical depictions of interventions in the CHE-trial.** Components are regarded either as objects (represented by squares) or as activities (represented by circles) 
[30].

### Conventional information

At present in Denmark, no standards or guidelines as to information and guidance of patients with chronic hand eczema exist. The patients in the control group will receive conventional information, i.e. written information sheets, in relation to medical consultations and allergy tests.

### Measurement

Due to difficulties of measuring health behaviour, interventional efficacy is to be assessed by the clinical impact presumably brought about by the altered behaviour 
[27]. Hence, primary outcome variable is objectively assessed disease severity.

At the inclusion point, a baseline investigation of both control and intervention group is performed while collecting data demographics, medical history and predisposing factors of eczema disease, as well as information of occupational and leisure time related exposures. Wherever possible, questionnaires used in the trial are based on previously validated scales (see below). The variables will be re-evaluated at follow up after six months.

### Primary outcome

#### Objective severity of hand eczema

The primary outcome variable is the change from baseline (T_0_) to follow up in objectively assessed disease severity, which is evaluated clinically by a member of the intervention team. The assessment relies on the Hand Eczema Severity Index (HECSI) which is a validated scoring system developed to quantify severity of hand eczema. HECSI is a visual medical assessment and subjective symptoms of the patient, e.g. itch or pain are not included 
[31]. Inter-rater variability in the present trial will be evaluated by random checks where patients are scored twice independently and by different assessors.

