### Statistical plan and data analysis sample size estimation

Studies examining patient compliance by the use of intervention group and group of control patients are usually recommended to include a minimum of 60 participants in each group if an absolute difference in effect of 25% between groups is to be demonstrated at a probability of 80% 
[14]. Medication adherence is not easily measured in particular when it comes to dynamic conditions like eczema with treatment being a combination of a topical pharmaceutical and preventive behaviour 
[43]. Also, power calculation is hampered by uncertainty of whether an individual action plan may promote a clinically improvement when under the influence of exogenous factors related to the patient. In a previous study that used HECSI-score as outcome variable an average score of 11.2 was detected at six months follow-up compared to an average score of 19.9 at baseline (n = 366) 
[44]. With reference to this follow-up score in the control group and assuming an improvement of 30% due to the intervention, a power calculation carry out a sample size need of at least 87 patients in each group. In details, the sample size is calculated based upon the following values at six months follow-up along with estimated standard deviations: Control group mean-HECSI 11 (SD 9.0) and Intervention group mean-HECSI 7.7 (SD 6.0). Applying an alpha error level at 5%; and a beta error level at 90%, the use of 2-samples average data input bring forward a need of 87 participants in each group to detect a difference (http:/www.ddsresearch.com/toolkit/sscalc/size_a2.asp).

With a 15% excess of the number due to non-parametric variables and with caution due to the heterogeneities of the sample, and to the probability of dropouts, it has been assessed that inclusion of 150 patients in each group may be sufficient to show the anticipated effect of the intervention in question. No studies with estimated sample sizes based on ‘the minimal clinically importan difference’ of life quality measures have been identified. However, when using SF-36 as efficacy variable a minimum of 71 patients in each group are requested in order to demonstrate an achieved effect size of 0.5 
[45]. Others propose a minimum of 80 in each group in interventional studies, targeting changes in health behaviour 
[46]. Hence, both figures are within the range of the present estimated sample size.

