### Statistical methods

All data obtained at baseline will be given a coded ID-number before they are used in further statistical analyses. After double data entry and with the guidance of a statistician, statistical analysis will be performed in SPSS. Stratification for relevant confounders will be performed and descriptive statistics as well as multivariate analyses will be conducted. Ordinal scaled data will be evaluated as to a Gaussian distribution after which between-group differences will be tested in accordance by the use of *t*-test or non-parametric test. Dichotomous efficacy variables are tested by use of chi^2^ test or exact test in case of small numbers. The significance level will be a p-value of less than 0.05.

The final number of patients included in the trial will be reported and intention-to-treat analyses are to be performed meaning all participants will be included in the analysis irrespective of compliance with the intervention protocol. However, an additional per-protocol analysis will also be conducted. Data from patients who refused to participate, dropouts, and loss-to-follow-up participants will be entered to an analysis based upon demographics in order to consider selection bias when interpreting the results. The presentation of the trial results will be according to the CONSORT statement to Trials of Nonpharmacologic Treatment 
[47].

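### The sample size is based on six-month HECSI scores, while the declared primary outcome is change from baseline; the stated power basis does not carry over, and baseline adjustment should be fixed as the primary analysis

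*Protocol article*

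**What the plan says.** Under Primary outcome (Objective severity of hand eczema), the protocol article declares: "The primary outcome variable is the change from baseline (T_0_) to follow up in objectively assessed disease severity". HECSI is the instrument, and it is scored before randomisation and again at six months.

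The sample size section works on a different scale: "the sample size is calculated based upon the following values at six months follow-up along with estimated standard deviations". The values are "Control group mean-HECSI 11 (SD 9.0) and Intervention group mean-HECSI 7.7 (SD 6.0"), obtained by "assuming an improvement of 30% due to the intervention". The source for the control value is an earlier study in which "an average score of 11.2 was detected at six months follow-up compared to an average score of 19.9 at baseline (n = 366"). The error rates are given as "Applying an alpha error level at 5%; and a beta error level at 90" per cent, and the result is "a power calculation carry out a sample size need of at least 87 patients in each group". This is then raised to 150 per group for non-parametric variables, heterogeneity of the sample and dropout.

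Under Statistical methods, after a check of the distribution, "between-group differences will be tested in accordance by the use of" a t-test or a non-parametric test. The same section promises stratification for confounders and multivariate analyses, without naming covariates or saying which analysis is primary.

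**The concern.** The variance of a change score includes the spread of the baseline score and depends on the correlation between the two measurements. The article gives neither quantity, so the SDs of 9.0 and 6.0 cannot stand in for the SD of change.

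The article's own figures suggest that change could be the noisier scale. The baseline mean in the earlier study is nearly twice the six-month mean (19.9 against 11.2), and the planning SDs rise with the mean (9.0/11 = 0.82; 6.0/7.7 = 0.78). If that pattern holds at baseline, the baseline SD is well above 9.

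At stake is precision. An unadjusted comparison of change is unbiased under randomisation, but it could have clearly less power than the plan supposes. Chance baseline imbalance in a variable score would also pass into the estimate, since randomisation is stratified by setting and gender only.

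**Working it through.** **Inputs from the article.** Six-month means 11 and 7.7 (difference 3.3); SDs 9.0 and 6.0; alpha 5%, taken as two-sided; the 90% beta error level, read as 90% power; 87 calculated and 150 planned per group; baseline mean 19.9.

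**Assumed, because the article does not give them.** Baseline SD s0 (same in both arms) and correlation r (same in both arms). All 150 per group are analysed unless stated.

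**1. The plan's own figure.** n = (SD1² + SD2²)(z_alpha + z_beta)² / d², with SD1² + SD2² = 81 + 36 = 117 and d² = 3.3² = 10.89.
- Two-sided, 90%: 117 × 10.507 / 10.89 = 112.9, so 113 per group.
- Two-sided, 80%: 117 × 7.849 / 10.89 = 84.3, so 85 (86 with the t distribution).
- One-sided, 90%: 93.
- Power at 87 per group: Phi(3.3/√(117/87) − 1.96) = Phi(0.886) = 81%.
- Power at 150 per group: Phi(3.3/√(117/150) − 1.96) = Phi(1.777) = 96%.

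The 87 does not reproduce at 90% power; it fits about 80% two-sided. The planned 150 exceeds 113.

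**2. Unadjusted change.** Randomisation makes the expected baseline means equal, so the expected difference in change is still 3.3. The variance per arm is s0² + s1² − 2·r·s0·s1. Summed over the arms this is V = 2·s0² + 117 − 30·r·s0, and power = Phi(3.3/√(V/150) − 1.96).

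Example, s0 = 12 and r = 0.5: V = 288 + 117 − 180 = 225; Phi(3.3/1.225 − 1.96) = Phi(0.735) = 77%.

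| Baseline SD (assumed) | r = 0.3 | r = 0.5 | r = 0.7 |
|---|---|---|---|
| 9 | 82% | 92% | 99% |
| 12 | 65% | 77% | 90% |
| 16.3 | 44% | 52% | 64% |

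The last row applies the plan's control SD/mean ratio to the baseline mean: 19.9 × 9/11 = 16.3.

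Change is noisier than the six-month score whenever 2·s0² > 30·r·s0, that is, s0 > 15·r: above 7.5 at r = 0.5, above 10.5 at r = 0.7. At r = 0.5, power drops below 90% once s0 passes about 9.5 and below 80% once it passes about 11.5.

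**3. Rank test on skewed scores.** Simulation with lognormal scores rounded to integers, the plan's six-month means and SDs, baseline SD 16.3 and 150 per group. At log-scale correlations of 0.4 to 0.7, a rank test on change has about 65–80% power; a t-test on the same data has about 45–60%.

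**4. Baseline-adjusted analysis.** For ANCOVA with a common slope, the residual variances sum to 117 − 112.5·r², whatever s0 is. At r = 0.5: 117 − 28.1 = 88.9; power = Phi(3.3/√(88.9/150) − 1.96) = Phi(2.33) = 99%. At r = 0.3 and 0.7 it is 97% and above 99%. For 90% power it needs about 103, 86 and 60 per group at r = 0.3, 0.5 and 0.7.

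**5. Loss to follow-up.** The article states no rate. If 15% were lost (about 128 per group), the unadjusted change comparison with s0 = 16.3 would have 39%, 46% and 57% power at r = 0.3, 0.5 and 0.7; the unadjusted six-month comparison would have 93%.

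**The case against.** A reader might infer that the trial has only about half the power it needs. The article does not support that. The 52% requires a baseline SD of 16.3, extrapolated from two estimated follow-up SDs, together with an assumed correlation of 0.5. If the baseline SD is 9 and the correlation 0.5, power is 92% and there is no shortfall. Moreover, a non-negative score with mean 19.9 and SD 16.3 is strongly skewed, so the article's own rule would lead to the rank test, which loses less. Both objections stand, and power has to be shown as a range.

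A reader might also infer that the primary outcome will be tested without baseline adjustment. That is not stated. Multivariate analyses are planned with unnamed covariates, a full analysis plan may specify them, and naming change as the outcome does not rule adjustment out: ANCOVA on change with baseline as covariate gives the same treatment estimate as ANCOVA on the six-month score. What can be said is that the only between-group test named for score data is unadjusted.

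Nor is change always the worse scale. If each arm had the same SD at baseline as at follow-up and the correlation exceeded 0.5, unadjusted change would have more power than the unadjusted six-month score.

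None of this removes the mismatch between the sizing scale and the outcome scale. The increase from 87 to 150 does not address it, since the article attributes it to other causes.

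**Conclusion.** The point holds as a mismatch within the document: the primary outcome is change, the sample size is derived for the six-month score, and nothing given allows power for change to be calculated. This should be corrected. It concerns precision and coherence of the plan, not bias.

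Its size is uncertain. Across assumed baseline SDs of 9 to 16.3 and correlations of 0.3 to 0.7, a t-test on unadjusted change with 150 per group has between 44% and 99% power. The lower end rests on the SD/mean ratio holding at baseline and on use of the t-test. Under the article's follow-up SDs, baseline adjustment gives about 97% or more over the same correlations.

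The calculation has its own defect: 87 per group gives about 81% two-sided power, not 90%. The planned 150 makes up for this on the six-month scale, with 37 per group (about 25%) to spare above 113.

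**What to change.** - State one primary analysis: six-month HECSI (or, equivalently, change) compared between arms by ANCOVA with baseline HECSI as covariate. Use robust standard errors because the arm SDs differ, and specify in advance a transformation or a rank-based version if the scores are skewed.
- Report the adjusted mean difference with its 95% confidence interval. Keep raw change as description.
- Restate the sample size basis to match: six-month means and SDs, two-sided 5%, 90% power (not a beta of 90%), and 113 per group without adjustment. Add an explicit dropout assumption leading to 150.

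The cost is wording in the protocol and analysis plan. Baseline HECSI is already scored before randomisation, so no extra data or patients are needed. The change should be made before outcome data are examined by arm.

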### Secondary outcome

#### Quality of life

The patient’s subjective symptoms will be measured by Dermatology Life Quality Index (DLQI) and by parts of Impact of Skin diseases on Daily Life (ISDL). DLQI is a dermatology specific questionnaire of life quality which has been used globally since 1994. At the moment DLQI is the best validated instrument for measuring quality of life among dermatological patients 
[32]. However, DLQI is not reckoned to be adequate to evaluate the impact that chronic hand eczema has on daily life and being of the individual. ISDL is a newly developed multi dimensional instrument which only exists in an English version. So far, it has been validated to patients suffering from psoriasis and atopic dermatitis 
[33]. It includes questions of itching and scratching which both are frequent phenomena also when it comes to hand eczema and which is not noticeably covered by DLQI 
[33]. In addition, a self constructed Visual Analogue Scale (VAS) of perceived global burden of disease will be used.

#### Self-rated health status

As disease specific life quality presumably will be influenced by co-morbidity and life quality in general, a measurement of self-rated health will be conducted by use of the frequently used generic Health Status Questionnaire, Short Form (SF-36).

#### Patient competencies

Several factors might affect the prognosis of chronic hand eczema. These are included in the questionnaire i.e. literacy; motivation for medication adherence and the patient’s knowledge of causative exposure and management of hand eczema 
[11,13-15,34].

Literacy is evaluated from questions of the highest obtained education; Single-Item Literacy Screener; and self-rated reading proficiency 
[35-37]. Moreover, subjective action competence i.e. self-efficacy has been shown to determine changes in health behaviour 
[38]. Self-efficacy is measured at baseline through the Danish Version of the General Self-Efficacy Scale. This is an instrument which addresses self-efficacy as a concept related to personality traits 
[39]. Medication adherence will be evaluated by use of a Danish version of The Medication Adherence Report Scale (DMARS-4). This is a generic scale as yet solely validated to cancer patients in relation to their analgesic treatment 
[40]. In addition the two group’s primary medication adherence at follow up will be evaluated by gathering of register data from the Danish Medicines Agency 
[12]. Assessment of the patients’ own knowledge of exposures and management of their hand eczema will be carried out by use of parts of Nordic Occupational Skin Questionnaire (NOSQ-2002) 
[41]. This questionnaire is already available in a Danish version. Finally, the investigator has added a supplement of self-constructed questions regarding skin protection behaviour at follow-up.

#### Sick leave

Information of self-reported sick leave related to hand eczema both at baseline and at follow up will be obtained through the questionnaire.

#### Possible confounders

Several factors might affect self-management capabilities and the prognosis of disease thus are included in the questionnaire i.e. socio-economic status; perceived social support as well as depression and stress. In the data analysis a rough assessment of prevalent depression among participants is done by items included in the mental health sub-scale in SF-36 
[42].

### Statistical plan and data analysis sample size estimation

Studies examining patient compliance by the use of intervention group and group of control patients are usually recommended to include a minimum of 60 participants in each group if an absolute difference in effect of 25% between groups is to be demonstrated at a probability of 80% 
[14]. Medication adherence is not easily measured in particular when it comes to dynamic conditions like eczema with treatment being a combination of a topical pharmaceutical and preventive behaviour 
[43]. Also, power calculation is hampered by uncertainty of whether an individual action plan may promote a clinically improvement when under the influence of exogenous factors related to the patient. In a previous study that used HECSI-score as outcome variable an average score of 11.2 was detected at six months follow-up compared to an average score of 19.9 at baseline (n = 366) 
[44]. With reference to this follow-up score in the control group and assuming an improvement of 30% due to the intervention, a power calculation carry out a sample size need of at least 87 patients in each group. In details, the sample size is calculated based upon the following values at six months follow-up along with estimated standard deviations: Control group mean-HECSI 11 (SD 9.0) and Intervention group mean-HECSI 7.7 (SD 6.0). Applying an alpha error level at 5%; and a beta error level at 90%, the use of 2-samples average data input bring forward a need of 87 participants in each group to detect a difference (http:/www.ddsresearch.com/toolkit/sscalc/size_a2.asp).

With a 15% excess of the number due to non-parametric variables and with caution due to the heterogeneities of the sample, and to the probability of dropouts, it has been assessed that inclusion of 150 patients in each group may be sufficient to show the anticipated effect of the intervention in question. No studies with estimated sample sizes based on ‘the minimal clinically importan difference’ of life quality measures have been identified. However, when using SF-36 as efficacy variable a minimum of 71 patients in each group are requested in order to demonstrate an achieved effect size of 0.5 
[45]. Others propose a minimum of 80 in each group in interventional studies, targeting changes in health behaviour 
[46]. Hence, both figures are within the range of the present estimated sample size.

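### The stated 87 per group does not follow from its own inputs at 90% power: the two-sample formula gives 113 two-sided (93 one-sided), although the planned 150 per group remains adequate

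*Protocol article*

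**What the plan says.** All of the calculation is in the protocol article, section *Statistical plan and data analysis sample size estimation*.

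- The control mean comes from a previous study, in which "an average score of 11.2 was detected at six months follow-up compared to an average score of 19.9 at baseline (n = 366" patients. It is rounded to 11 for the calculation.
- The effect is set by "assuming an improvement of 30% due to the intervention".
- The resulting inputs are "Control group mean-HECSI 11 (SD 9.0) and Intervention group mean-HECSI 7.7 (SD 6.0").
- The error rates and result follow: "Applying an alpha error level at 5"%, then "a beta error level at 90%, the use of 2-samples average data input bring forward a need of 87 participants in each group".
- The article adds a 15% excess for non-parametric variables and an unquantified allowance for heterogeneity and dropout. It concludes that "it has been assessed that inclusion of 150 patients in each group may be sufficient".

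Under *Statistical methods*, the article says "The significance level will be a p-value of less than 0.05" and names a t-test or a non-parametric test. Neither section says whether the test is one- or two-sided. Under *Randomisation*, allocation is approximately 50:50.

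**The concern.** Every number needed to reproduce the calculation is printed, so the result can be checked without any other document. The inputs give clearly more than 87 at 90% power. The error statement also does not make sense as written: beta is the type II error, and a beta of 90% would be 10% power.

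Two things are at stake. First, the article links 90% power to a number that does not provide it on the stated inputs. Second, 87 is the base from which 150 is reached. If the base is too small, the distance from it to 150 looks like a larger reserve for dropout, heterogeneity and non-normality than the trial has.

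**Working it through.** **Inputs** (protocol article, sample-size section unless noted)

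- Difference: 11 − 7.7 = 3.3, which is 30% of 11, so the means agree with the assumed effect.
- Sum of variances: 9.0² + 6.0² = 81 + 36 = 117.
- Alpha 5%. Sidedness is not stated, so both are tried.
- Power 90%, reading the beta phrase as power.
- Equal allocation (*Randomisation*).

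**Formula.** For two means with unequal SDs, n per group = (SD₁² + SD₂²)(z_alpha + z_power)² / difference².

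**Attempt to reproduce 87**

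| Test | Power | Calculation | n per group |
|---|---|---|---|
| Two-sided 5% | 90% | 117 × (1.960 + 1.2816)² / 3.3² = 112.9 | 113 |
| One-sided 5% | 90% | 117 × (1.645 + 1.2816)² / 3.3² = 92.01 | 93 |
| Two-sided 5% | 80% | 117 × (1.960 + 0.8416)² / 3.3² = 84.3 | 85 |
| One-sided 5% | 80% | 117 × (1.645 + 0.8416)² / 3.3² = 66.4 | 67 |

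With the t distribution in place of the normal approximation, the two-sided figures become 114–115 (90%) and 86 (80%). The stated 87 is not obtained at 90% power under either sidedness. It lies close only to the two-sided 80% figure.

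**Other routes to 87 at 90% power.** Each needs an unstated one-sided test and at least one further departure from the printed inputs:

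- averaging the two SDs to 7.5: 89;
- using 30% of the unrounded 11.2, a difference of 3.36: 89;
- both together: 86.

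**Power at 87 per group**

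- Standard error of the difference: √(117/87) = 1.160. Standardised difference: 3.3 / 1.160 = 2.846.
- Two-sided: Φ(2.846 − 1.960) = Φ(0.886) = 81.2% (80.7–80.8% with the t distribution).
- One-sided: Φ(2.846 − 1.645) = Φ(1.201) = 88.5%.

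**Power at the planned 150 per group, no loss, two-sided**

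- √(117/150) = 0.883; 3.3 / 0.883 = 3.736; Φ(3.736 − 1.960) = Φ(1.776) = 96.2%.
- If the 15% excess is treated as the cost of a rank test, 150 / 1.15 = 130.4 effective per group; √(117/130.4) = 0.947; Φ(3.3/0.947 − 1.960) ≈ 94%.

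**Margin between the base and 150, if all of it is assigned to dropout**

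| Base | Without the 15% excess | With the 15% excess |
|---|---|---|
| 87 (as printed) | 1 − 87/150 = 42% | 87 × 1.15 = 100; 1 − 100/150 = 33% |
| 113 (recomputed, two-sided) | 1 − 113/150 = 25% | 113 × 1.15 = 130; 1 − 130/150 = 13% |

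**The case against.** **Enrolment is not 87.** The trial plans 150 per group, which exceeds 113 and also exceeds 130. No analysis, decision rule or enrolment target depends on 87 once 150 is fixed. This stands, and it limits the consequence.

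**Sidedness is not stated.** The figure of 113 rests on a two-sided test. That is the convention for a 0.05 threshold with these tests, but the article does not write it, and its hypothesis is directional. If a one-sided 5% test was meant, the shortfall is small: 93 against 87, or 88.5% power against 90%. This stands as a qualification, but the printed number is still not reproduced.

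**The wrong element may be the power.** Since 87 is close to the two-sided 80% figure, the power may have been misreported and the number may be as intended. The article does not settle this, so the correction should leave either route open.

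**No dropout tolerance is claimed.** A reader might infer that the plan promises to absorb a one-third loss, because 87 with 15% added is 100 and 100 is two-thirds of 150. The article gives no dropout rate or tolerance, and it assigns the margin to heterogeneity as well. The percentages in the margin table are therefore upper limits under a stated assumption and are not the plan's own figures. A reader might also picture a null result at 87 evaluable per group being taken as 90%-powered. That would need a 42% loss from 150, which the article nowhere anticipates.

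**The calculation uses six-month scores.** The primary outcome is change from baseline, whereas the calculation uses follow-up means and SDs. The figures here correct the calculation as printed and do not re-size the trial for the change score.

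**Conclusion.** The stated sample size is wrong as written. With the printed means, SDs and alpha, 90% power needs 113 per group two-sided or 93 one-sided; 87 per group gives about 81% or 88.5% respectively. The beta phrase is a separate wording error. These results rest on the normal approximation (the t distribution moves them by one or two patients), on equal groups, and on reading the beta phrase as 90% power.

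A reader might conclude that the trial is underpowered. The documents do not support that: on the plan's own assumptions, 150 per group gives about 96% two-sided power with no loss, and 113 evaluable per group remain after a loss of up to about 25%. The error is confined to the stated derivation and power, and to a margin that is smaller than the base of 87 suggests.

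**What to change.** State the sidedness of the test, replace the beta phrase with power 90% (beta 10%), and correct whichever figure is inconsistent:

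- **Correct the number:** two-sided alpha 5%, power 90% (beta 10%), 113 evaluable per group, or 130 with the 15% non-parametric excess; or
- **Correct the power:** 87 per group gives about 81% power with two-sided alpha 5%.

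If a one-sided test was intended, say so and give 93 per group for 90% power, or 88.5% power at 87.

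Keep 150 per group. Add that it gives about 96% two-sided power with no loss, and that the margin for dropout and heterogeneity is at most about 25% over a need of 113, or about 13% over a need of 130, if all of it is assigned to dropout.

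The cost is wording only: no extra patients and no change to the analysis. The reserve described becomes less generous.
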